### Evaluation procedures

#### Aim 1 implementation progress

Data includes benchmark scores rated by the site coordinating committee every 6 months, with results reported to community leaders and other implementation partners. Summary benchmark indicators can be displayed using simple bar-graphs and maps, so patterns can be easily recognized by community members, implementation partners, and researchers. The benchmark information from all three sites can be summarized and tracked. Health centre data will be used to track changes over time in the number of condoms distributed, HIV tests requested and related services provided in clinics serving the three communities.

#### Aim 2 implementation patterns

Patterns will be assessed using qualitative data from our study team’s observations, notes of meetings they attend, and annual individual and focus group interviews. Interviews will include persons who have been either highly enthusiastic (e.g., “champion” in the District Advisory Committee, an especially “productive” peer leader) or unenthusiastic (e.g., person who expressed reservations about the peer group contents, peer leader who discontinued participation). Quantitative measures include the benchmarks described above and independent evaluations of Mzake fidelity by the research team.

#### Aim 3 effectiveness measures

Following the stepped wedge design [28, 42, 43], all adult and youth participants are recruited and consented at Wave 1 (baseline). The data collection procedure is the same for each wave. Each participant completes a brief Audio Computer-Assisted Self-Interviewing (ACASI) survey four times (Waves 1–4). We used ACASI in a previous study with young women with no problems. ACASI promotes privacy and higher reporting of sensitive sexual behaviors [44]. and was well-received by participants. To retain participants in the repeated surveys, we use standard retention strategies, including respectful interactions, repeated telephone contacts when necessary, refreshments and a small cash allowance for travel and associated.

We originally planned to obtain STI biomarkers (as indicators of unprotected sex) using rapid tests to assess the presence of three prevalent sexually transmitted infections (STIs; gonorrhea, chlamydia, and syphilis) at two time points. However, several recent studies found that the non-invasive rapid tests for gonorrhea and chlamydia had unacceptably low reliability and one was withdrawn from the market [45, 46]. Instead, we substituted a detailed systematic STI symptoms interview recommended by [name]. In her Kenya research, she found that interviews by a nurse were accurate in identifying who had an STI based on laboratory follow-up (personal communication, 11/23/2015). The nurse will refer anyone with current symptoms and follow-up within a week to ensure compliance. We discussed the planned protocol modification with our program officer at the National Institutes of Health and obtained approval. We then modified the protocol in clinicaltrials.gov.

#### Aim 4 integration

Integration of implementation patterns with effectiveness and sustainability will use all of the above data. No new data are collected for this aim.

### Analysis

#### Data management and iterative analysis

Throughout the study, analysis is continuous and iterative, integrating new data as they become available. Data management protocols promote proper and timely preparation of data for analysis and secure data storage. All data are identified by location and date. A unique individual code is assigned to Individual-level data, including effectiveness evaluation data and individual interviews. Master lists linking names and code numbers will be securely stored separately from the data. Only de-identified data will be transferred from Malawi to UIC using a secure transfer system. *Quantitative data* collected include the benchmarks, Effectiveness Evaluation surveys and STI tests. The ACASI survey data are automatically entered into a database. All other data are entered by data clerks with 100% verification and transferred to data analysis programs (SAS, SPSS). *Qualitative data* (hand-written study notes and audio-recorded focus groups and individual interviews) are processed following Huberman and Miles’ recommended strategies to code, store, and retrieve data [47]. Recorded interviews and hand written notes are typed from notes or transcribed verbatim, referring to the original recordings to verify accuracy of the typed transcripts. Materials in Chichewa are translated using the same translation process described above in Measures. Transcripts and notes are imported into a qualitative data management and coding program that accepts quantitative as well as narrative data.

#### Aim 1 (implementation progress)

We examine whether each site is using the 3-Step Model to implement the program and the extent and fidelity of implementation. We will analyse progress through changes in the benchmark scores across time within each site. We then examine the similarities and differences in progress across sites. Fidelity to the model is assessed by examining whether the steps of the 3-Step Model are being followed in the recommended order, adapted or skipped (e.g., variation in steps). *When Aim 1 analysis is complete, we will have a description of how implementation has unfolded at each site over time and across sites, including which sites continued implementation, amount of implementation, and degree of fidelity to the 3-Step Model.*

#### Aim 2 (implementation patterns)

We use mixed methods analysis to examine the patterns that emerge over time and across sites and the contextual factors that influence these patterns. Qualitative data are coded based on the conceptual frameworks that underlie the 3-Step Model and *Mzake* [21, 36]. We focus on reported successes, challenges, solutions tried and whether successful, as well as champions and naysayers who emerge. We will be sensitive to new discoveries that emerge, which will be developed into new codes. Final codes are compiled in the master codebook and applied to the coding of all qualitative date. The data will be double-coded until intercoder reliability exceeds 85%. Thereafter, 20% of randomly selected materials will be double-coded.

We use quantitative descriptive statistics for initial analysis of the benchmarks and fidelity assessments [22, 37]. The benchmarks provide a way to assess fidelity to the 3-Step Model and contextual adaptation, as described above (Aim 1). Fidelity to *Mzake* is assessed using a simple rating by the peer leader. During this implementation study, the peer leader self-ratings will be validated using periodic independent detailed observation by the research team. If the peer leader self-ratings correlate with our observations, self-ratings can be used by communities to monitor fidelity independently. Comparing fidelity scores with those found in the *Mzake* efficacy study provides a standard for the level of fidelity sufficient to produce the desired outcomes. We will compute the fidelity score for each group observed. We will then create three mean fidelity scores at each site, overall fidelity, early fidelity (during roll-out) and later fidelity. We expect peer leader early fidelity to be acceptably high and to increase over time as sites and peer leaders gain experience. We will also describe variations by peer group gender and age category (youth or adult). For each site, we will annually produce a case summary including both qualitative and quantitative data summarizing processes and contextual factors affecting implementation.

Finally we integrate these different data using well-established mixed methods analyses as described by Cresswell [48] and Greene [49], in which both qualitative and quantitative data are transformed into comparable categorical or interval-level data. These data are then brought together using within and across case matrices that allow identification of co-occurrences, patterns and variations [47, 48, 50]. Throughout the mixed methods analysis, we will observe the ways in which communities balance fidelity to the core components of the intervention and adaptations that make the intervention work for their context. *At the conclusion of the analysis for Aim 2, we will identify the major implementation patterns and consistency and variation across sites and time.*

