### Measures

This mixed-methods evaluation uses multiple types of data from different sources. Table 1 below summarizes the data sources and measures. Most materials are already translated, but new materials are translated using a team approach throughout the study. After initial translations and back-translations, a translation team (bilingual nurse, academic, and lay persons) reach consensus regarding differences, ensuring that the materials are accurate, comprehensible and conceptually equivalent [38–41].

**Table 1 Tab1:** Evaluation measures

Aim	Measures
1. Implementation progress	
Benchmarks	26 yes/no items (1 point for each done) measuring implementation progress at each site. Numeric summaries are also recorded for peer leaders trained, 7-session peer groups and boosters held (# completed, # of adult and youth participants). Scored every 6 months. Summaries for each community and the total are presented to the community and district leaders and integrated with related local health outcome data (e.g., # of HIV tests provided, % of pregnant women tested) routinely collected and provided by the District Health Officer.
2. Implementation patterns and process	
Peer group fidelity ratings	• Structured fidelity ratings by the Research team (trained to an inter-rater reliability of 0.85) [37]. At least one of the early sessions of all peer leaders plus randomly selected groups thereafter is observed. • Peer leaders’ self-assessments and attendance sheets
Observation notes on meetings	Study notes by the research team (semi-structured observations of all meetings attended) documenting type of meeting or observation, date, site, and discussion related to successes, challenges, if problem was solved; and personal interactions
Annual focus group & Individual Interviews	7–12 focus group interviews with district and community implementation partners and 8–12 individual interviews with implementation partners including local “champions” and unsupportive individuals. Coded to identify successes, problems/barriers/ solutions, and appraisal of support and technical assistance
3. Effectiveness for Participants	

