#### Implementation at 3 sites

We test the 3-Step Model in the 3 sites sequentially, with the order of introduction at each site randomly assigned during a public meeting. The same sequence of implementation steps and activities occurs at all sites.

During the *Prepare* step (2 months), community leaders are oriented to the program and form a site coordinating committee comprised of respected adults active in community affairs. The committee is oriented to the 3-Step Model and *Mzake.* They learn about the benchmarks which they use to develop a plan and evaluate progress every 6 months (Table 1). After making a community implementation plan, they recruit volunteers to become peer leaders. The volunteers are trained to deliver *Mzake,* maintain group records and complete a brief self-evaluation of fidelity. *The primary capacities built during this period are conceptual understanding of the* 3-Step Model *and Mzake; planning and coordination for the coordinating committee and peer group leadership skills for peer leaders.*

During *Roll-Out* (8 months), *Mzake* is introduced to community members at village meetings and those who are interested sign up to be in the peer groups and complete informed consent. The first 144 participants must also agree to complete the repeated effectiveness surveys. Peer leaders conduct the first round of 12 groups with adults, then reflect on their experiences with the coordinating committee and make any modifications. Because talking about sexuality with youth is a sensitive topic in Malawi, the leaders obtain experience and confidence with adult groups and then the same peer leaders offer 12 groups with youth. During both adult and youth groups, the research team rates fidelity and provides supportive coaching for each pair of leaders during at least one early session and one later session, rating fidelity and providing coaching to the leaders. After these initial peer groups are completed, the peer leaders and committee will meet to reflect on lessons learned and prepare for future implementation. The lessons learned from both rounds of groups will be shared with implementation partners and iteratively used to modify the 3-Step Model. *The primary capacities built during this period are: experience in using the* 3-Step Model *and offering Mzake, practical logistics for local implementation and completing the benchmarks self-evaluation for committee members.*

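### Peer-leader self-ratings of fidelity can be approved for independent community use on correlation alone, which does not detect uniform or near-uniform over-rating

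*Protocol article*

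**What the plan says.** All of this is in the protocol article.

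- Under Analysis, Aim 2 (implementation patterns), fidelity to the peer-group programme "is assessed using a simple rating by the peer leader".
- That section adds that "the peer leader self-ratings will be validated using periodic independent detailed observation by the research team".
- It then states the decision rule and its consequence: "If the peer leader self-ratings correlate with our observations, self-ratings can be used by communities to monitor fidelity independently".
- The next sentence says that comparing fidelity scores with those of the efficacy study "provides a standard for the level of fidelity sufficient to produce the desired outcomes".
- For the study's own summaries it says: "We will compute the fidelity score for each group observed". Three mean scores per site follow (overall, early, later).
- In Table 1 (Measures), the research-team raters are "trained to an inter-rater reliability of 0.85".
- Under Implementation at 3 sites, the research team rates fidelity and "provides supportive coaching for each pair of leaders during at least one early session and one later session".

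The article gives no coefficient, threshold, mean difference, agreement statistic or calibration for comparing leader with observer. It also does not say whether the two ratings share a scale.

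**The concern.** The rule tests agreement in rank order. The standard in the sentence after it is a level. A self-rating can track the observers closely from group to group and still sit well above them throughout, and a correlation cannot reveal that.

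The reliability of 0.85 does not close the gap, because it applies between research-team raters and not between leader and observer.

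What is at stake is the hand-over of monitoring. Research-team support is meant to decrease, and the article plans 30, 18 and 8 months of independent sustaining at Sites 1, 2 and 3. If self-rating is approved for independent use, a community that relies on it would have no built-in sign that its scores run high.

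**Working it through.** The article states no figure for this validation, so there is none to reproduce. The check is of what the rule can and cannot detect. Every numerical input below is an assumption.

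**1. Uniform shift.** Take observer and self scores with equal spread, correlation r, and self-ratings higher by d standard deviations.

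- Pearson correlation: r, whatever the value of d.
- Lin's concordance coefficient: 2r / (2 + d²).
- Share of groups self-rated below the standard: Φ(z − d), where Φ(z) is the share truly below it.

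With r = 0.80:

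| Over-rating d | Correlation | Concordance |
|---|---|---|
| 0 | 0.80 | 1.60 / 2.00 = 0.80 |
| 0.5 SD | 0.80 | 1.60 / 2.25 = 0.71 |
| 1 SD | 0.80 | 1.60 / 3.00 = 0.53 |

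For normally distributed scores and d = 1:

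- 30% truly below: z = −0.524, Φ(−1.524) = 0.064, so about 6% are self-rated below.
- 50% truly below: z = 0, Φ(−1) = 0.159, so about 16% are self-rated below.

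The share of truly low groups that self-rating flags, from the bivariate normal distribution with r = 0.80:

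| Over-rating d | 30% truly below | 50% truly below |
|---|---|---|
| 0 | 70% | 80% |
| 0.5 SD | 43% | 56% |
| 1 SD | 20% | 31% |

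**2. Another scale and other correlations.** A simulation of 200,000 pairs assumed an observer mean of 75, an SD of 10 in both ratings, and a cut-off of 75. At r = 0.85, over-rating by 0, 5, 10 and 20 points left the correlation at 0.85. Concordance was 0.85, 0.76, 0.57 and 0.28. The share of below-standard sessions that looked adequate was 18%, 42%, 69% and 95%. At r = 0.50 that share was 33%, 55%, 74% and 96%.

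**3. Over-rating that is not uniform.** Take an observer SD of 10, a mean over-rating of 10 points and residual error of SD 5.

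- Leaders differ in their over-rating with SD s: r = 10 / √(100 + s² + 25). This is 0.89 for s = 0, 0.82 for s = 5 and 0.67 for s = 10.
- Weaker leaders over-rate more, so that self-rating rises with observer score at slope b: r = 10b / √(100b² + 25). This is 0.71 for b = 0.5 and 0.37 for b = 0.2.

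The correlation does register uneven over-rating, and strongly so when it is concentrated in the weaker leaders. How low it must fall before approval is refused is not stated.

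**The case against.** The strongest reply has five parts.

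- **Scope of the standard.** Fidelity scores are computed for observed groups, so the comparison with the efficacy study is most naturally made with observer scores. The article does not say that communities will hold self-ratings to that level. If they use them to follow change or find weaker groups, rank order is relevant evidence. This stands: the level-based use is inferred from the two adjacent sentences. But the article presents that level as the mark of sufficient fidelity, and a self-rating approved on correlation alone could not be read against it.
- **Reach.** A reader might infer that biased self-ratings contaminate the site fidelity means, the effectiveness results or the Aim 4 integration. The documents do not support this. The site means rest on observed groups, and the Aim 3 model does not use self-ratings. The fidelity named in the Aim 4 analysis is to the 3-Step Model, which is assessed through steps and benchmarks.
- **Certainty.** A reader might also infer that any systematic over-rating would pass. That holds only for uniform or near-uniform bias, as step 3 of the working shows.
- **Feasibility.** The self-rating is simple and the observation detailed. No common scale is stated, nor that each observed session has a matching self-rating. An agreement statistic may therefore not be computable directly. This stands and shapes the fix.
- **Condensed reporting.** The choice of statistic could sit in a fuller document, and descriptive statistics are planned for the fidelity assessments. These might show a level difference. The article nevertheless states a condition and its consequence, and agreement in level is not part of the condition.

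**Conclusion.** The concern holds in a limited form. As stated, the rule could approve self-ratings for independent community use although they run uniformly or nearly uniformly high and cannot show whether a group reaches the efficacy-study level. Only the conclusion about independent community monitoring is at risk.

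The size cannot be taken from the article. The concordance of 0.53 and the fall from 30% to about 6% rest on equal spread, normal scores, r = 0.80 and a uniform 1 SD shift. They show what the rule can miss and do not forecast what will happen. The point is worth correcting, but it does not threaten the primary outcomes.

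**What to change.** Keep the correlation, and make approval also depend on agreement in level, using self and observer ratings matched on the same observed sessions.

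- If the two ratings share a scale, require the mean difference with its limits of agreement, or an absolute-agreement intraclass correlation, to lie within bounds set beforehand.
- If they do not, either calibrate the self-rating to the observer score or require a pre-set level of agreement on adequate versus inadequate at the efficacy-study level.
- In both cases, report the share of observer-rated low-fidelity sessions that self-rating also flags.

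The cost is a few sentences of analysis wording, plus making sure that a self-rating exists for each observed session and can be linked to it. Both kinds of rating are already planned, but the article does not say that they are matched. The criterion is harder to meet than correlation alone.

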*Sustaining* is divided into two periods, 11 months of sustaining with partial support, followed by independent sustaining up to the last year of the grant period. Because of the staggered implementation plan, Site 1 will have 30 months of independent sustaining, Site 2 will have 18 months and Site 3 will have 8 months of independent sustaining. During sustaining with support, sites are told that they will receive a specific amount of money for 11 months of sustaining activities. The committee members receive advanced training regarding sustaining and discuss their vision for what should happen. They receive additional guidance on planning activities, budgeting for them and accounting for expenditures. Activities during sustaining include training more peer group leaders and possibly new committee members, holding *Mzake* groups for new participants and in new areas, and booster activities for those who have already attended *Mzake*. One important part of sustaining is ensuring the capacity to train new peer group leaders, and the committee may decide to ask for training of interested peer leaders as trainers. They then decide how to allocate their efforts and carry out their plans, monitoring what is happening and making any needed adjustments. Toward the end of sustaining with support, the committee learns how to write a proposal and budget in a workshop and seeks funding from us and other sources. Our staff is available but does not initiate regular contacts as we do during roll-out.

During independent sustaining, the community should begin to expand to new areas and obtain new support for their work. They can apply to us for a small grant and to the District Commissioner’s office and other funders for additional months of partial funding. The Study Team continues “hands-off” observation of progress during the remainder of this period [23]. The intention is for each community to continue indefinitely. However, we only observe progress up to Month 52. *The primary capacities built during this period are independently training new peer leaders, conducting booster sessions, expanding to new parts of their own site and possibly to other sites, maintaining financial records, and preparing proposals and budgets to sustain activities.*

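### Early and later Mzake fidelity are split by site phase, so their difference mixes leader experience with the entry of new leaders and cannot be read as leaders improving

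*Protocol article*

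**What the plan says.** Under Analysis, Aim 2 (implementation patterns), the protocol article scores fidelity by observed group ("We will compute the fidelity score for each group observed") and then averages by site: "We will then create three mean fidelity scores at each site, overall fidelity, early fidelity (during roll-out) and later fidelity". Early is thus tied to a phase of the site. Later is not defined further and is read here as after Roll-Out. The next sentence says what the team hopes to see: "We expect peer leader early fidelity to be acceptably high and to increase over time as sites and peer leaders gain experience". The analysis is described as descriptive: "We use quantitative descriptive statistics for initial analysis of the benchmarks and fidelity assessments".

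Three other statements determine which ratings enter which mean:

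- Implementation at 3 sites, on Roll-Out: during the adult and youth groups the research team visits "each pair of leaders during at least one early session and one later session, rating fidelity and providing coaching to the leaders". The same leaders run 12 adult groups and then 12 youth groups within this 8-month step.
- Measures, Table 1: "At least one of the early sessions of all peer leaders plus randomly selected groups thereafter is observed".
- Implementation at 3 sites, on Sustaining: "Activities during sustaining include training more peer group leaders and possibly new committee members, holding" further groups for new participants and in new areas.

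**The concern.** The expectation has two parts, sites gaining experience and leaders gaining experience, but the split follows only the site's calendar. A leader pair's progress from its early to its later Roll-Out session is averaged inside the early mean. A leader trained during Sustaining is a novice when first observed, yet that rating goes into the later mean. So the difference between the two means reflects who is leading groups in each phase as well as how leaders develop.

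What is at stake is interpretation. Training new leaders is an intended activity of Sustaining. A site that does so could show flat or falling mean fidelity although each of its leaders improves, and a site that trains no one new could show a rise. A reader who takes the difference as evidence about leaders' learning would be misled in either case.

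**Working it through.** The article gives no sample size, fidelity level or expected change for this comparison, so there is no figure of the plan to reproduce. The check first places each rating and then works out what the contrast measures.

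**Placing the ratings**

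| Rating | Leader's experience | Mean it enters |
|---|---|---|
| Original pair, early Roll-Out session | novice | early |
| Original pair, later Roll-Out session | experienced | early |
| Original pair, randomly selected group during Sustaining | experienced | later |
| New leader, first observed session during Sustaining | novice | later |

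The last row assumes that Table 1's rule covering all peer leaders includes those trained during Sustaining. Both means can therefore hold novice and experienced ratings.

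**Inputs (all assumed; the article gives none)**

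- F: a leader's fidelity in the first rated session.
- d: the gain with experience, the same for every leader.
- p: the share of later ratings that are new leaders' first sessions, from 0 to 1.
- One early and one later rating per original pair in Roll-Out, which is the stated minimum.
- No change at site level.

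**Formulae**

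- Early mean = [F + (F + d)] / 2 = F + 0.5d.
- Later mean = pF + (1 - p)(F + d) = F + (1 - p)d.
- Later minus early = (1 - p)d - 0.5d = (0.5 - p)d.

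**Two variants**

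- If only one of four Roll-Out ratings is a true novice rating (for example, leaders are already experienced when the youth groups start), the early mean is F + 0.75d and the difference is (0.25 - p)d.
- If a site-level gain of 0.25d is added in the later phase to the base case, the difference is (0.5 - p)d + 0.25d = (0.75 - p)d.

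| p | Base case | One novice rating in four | Base case plus site gain of 0.25d |
|---|---|---|---|
| 0 | +0.50d | +0.25d | +0.75d |
| 0.25 | +0.25d | 0 | +0.50d |
| 0.5 | 0 | -0.25d | +0.25d |
| 0.75 | -0.25d | -0.50d | 0 |
| 1 | -0.50d | -0.75d | -0.25d |

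The true gain per leader is d in every cell, and no cell returns d. In the base case, comparing each pair's first rating with its subsequent ratings gives (F + d) - F = d, whatever p is.

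**The case against.** The strongest reply is that the plan describes sites. The site is the case in Aims 1, 2 and 4, and fidelity delivered at a site during Roll-Out and afterwards is a legitimate thing to report. If a site expands with less practised leaders, its delivered fidelity really has fallen, and a scale-up study should show that. The expectation also names sites as well as leaders. Numbers of leaders trained are recorded, and the case summaries and matrices add context. This stands, and it is why the phase means should be kept. It does not make their difference a measure of leaders' learning, and the planned breakdown by group gender and age category does not separate original from new leaders.

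A second reply is that a condensed article may leave such stratification to a fuller document. But the article itself fixes the split and, in the next sentence, attaches an expectation about leaders that the split does not isolate.

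Four stronger readings are tempting, and the article does not support them:

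- That a planned test is invalid. No test, threshold or decision rule rests on this contrast.
- That the contrast could reverse which site looks successful in Aim 4. The worked example there concerns fidelity to the 3-Step Model, which is judged from benchmarks and the order of steps, not Mzake session fidelity.
- That withdrawal of coaching is an established third confounder. Roll-Out ratings are paired with coaching, and staff contact is reduced afterwards, but whether later ratings come without coaching is not stated.
- That a true gain will show as none. That happens only at particular values of p, such as p = 0.5 in the base case, and p is not given.

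**Conclusion.** The point holds as a minor one. The early-to-later difference in site means combines leader experience with leader turnover, so it should not be read as leaders improving or failing to improve. Without a site effect it understates the leader-level gain at every p, and it vanishes or reverses as the new-leader share grows.

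This rests on three things: later means after Roll-Out; leaders trained during Sustaining also have an early session rated; and gains are equal across leaders. If no new leaders were rated during Sustaining (p = 0), the reversal disappears, but the base-case contrast still shows only half the gain, because both scheduled ratings of the original pairs sit in the early mean. Roll-Out ratings are minimums and the number of Sustaining ratings is not stated, so the actual size and direction cannot be determined. The matter is confined to a descriptive Aim 2 measure; the Aim 3 effectiveness analysis is not affected.

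**What to change.** Keep the three site means and label them as fidelity delivered in each phase. Then:

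1. Compare the first with subsequent rated sessions within each leader pair, by age category (adult or youth) where the ratings allow. It is unclear whether each pair is rated early and later in both kinds of group, so this stratification may not always be possible.
2. Report Sustaining-phase fidelity separately for original and newly trained leaders, with the number of ratings in each.
3. Record the leader pair identifier and session number with every rating, and keep session-level scores before averaging to the group. The data management section promises only location and date for all data, so this needs to be confirmed.
4. Compare both Roll-Out fidelity and the stratified Sustaining fidelity with the efficacy-study standard. Roll-Out fidelity should stay in that comparison because it is what the Aim 3 cohort received.

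No additional observations are needed; the cost is analysis time and two identifiers per rating. The drawback is few sessions per stratum at each of three sites, so the results should remain descriptive and show their counts.
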